## Abstract

**Background:**

Our knowledge of immune-mediated inflammatory disease (IMID) aetiology and pathogenesis has improved greatly over recent years, however, very little is known of the factors that trigger disease relapses (flares), converting diseases from inactive to active states. Focussing on rheumatoid arthritis (RA), the challenge that we will address is why IMIDs remit and relapse. Extrapolating from pathogenetic factors involved in disease initiation, new episodes of inflammation could be triggered by recurrent systemic immune dysregulation or locally by factors within the joint, either of which could be endorsed by overarching epigenetic factors or changes in systemic or localised metabolism.

**Methods:**

The BIO-FLARE study is a non-randomised longitudinal cohort study that aims to enrol 150 patients with RA in remission on a stable dose of non-biologic disease-modifying anti-rheumatic drugs (DMARDs), who consent to discontinue treatment. Participants stop their DMARDs at time 0 and are offered an optional ultrasound-guided synovial biopsy. They are studied intensively, with blood sampling and clinical evaluation at weeks 0, 2, 5, 8, 12 and 24. It is anticipated that 50% of participants will have a disease flare, whilst 50% remain in drug-free remission for the study duration (24 weeks). Flaring participants undergo an ultrasound-guided synovial biopsy before reinstatement of previous treatment. Blood samples will be used to investigate immune cell subsets, their activation status and their cytokine profile, autoantibody profiles and epigenetic profiles. Synovial biopsies will be examined to profile cell lineages and subtypes present at flare. Blood, urine and synovium will be examined to determine metabolic profiles. Taking into account all generated data, multivariate statistical techniques will be employed to develop a model to predict impending flare in RA, highlighting therapeutic pathways and informative biomarkers. Despite initial recruitment to time and target, the SARS-CoV-2 pandemic has impacted significantly, and a decision was taken to close recruitment at 118 participants with complete data.

**Discussion:**

This study aims to investigate the pathogenesis of flare in rheumatoid arthritis, which is a significant knowledge gap in our understanding, addressing a major unmet patient need.

**Trial registration:**

The study was retrospectively registered on 27/06/2019 in the ISRCTN registry 16371380.

## Background

Rheumatoid arthritis (RA) is a relapsing and remitting autoimmune disease characterised by chronic, polyarticular joint inflammation, disability and premature mortality [1]. Recent epidemiological studies have provided critical aetiological insights that clearly invoke environmental factors, such as cigarette smoking, interacting with an immunogenetic predisposition to trigger breach of tolerance – which, several years later, transitions from asymptomatic ‘pre-RA’ to clinical disease [2, 3]. Once established, the course of RA is usually characterised by episodes of disease remission interspersed with periods of active inflammation, despite the use of synthetic and biological therapies. The pathophysiology of RA remains incompletely understood, but a picture in which disruptions of immune, stromal and epigenetic pathways all contribute to a breakdown in self-tolerance has emerged [4]. However, it is important to note that almost all data underpinning this model are derived from patients with active established disease. In contrast, much less is known about RA in remission and virtually nothing about the processes operating during the transition from remission to flare. This remains a substantially under-investigated area that the BIO-FLARE study aims to address. An understanding of this aspect of RA pathogenesis will prove useful in preventing and treating flares. Beyond this, however, it could also provide insights into the genesis of clinical RA, the critical initiating events wherein the immune system and stroma interact to generate chronic synovial inflammation during the transition from pre-RA to RA (Fig. 1).

**Fig. 1 Fig1:**
[figure not shown]
RA Aetiopathogenesis. Environmental factors act upon genetic predisposition to cause breach of tolerance (transition A); Unknown factors act on an individual with pre-RA to trigger active RA (transition B); Treatment induces remission (transition C); Unknown factors trigger flare (transition D). Colours denote what is well investigated (green), the focus of the study (orange) and additional processes that this study could inform (pink)

The underpinning mechanism(s) of flare have been difficult to study because they occur unpredictably. However, we have recently established a highly relevant human model that generates a ‘synchronized’ population of RA patients in clinical remission, approximately 50% of whom relapse within 6 months, the remainder maintaining remission. The Biomarkers of Remission in Rheumatoid Arthritis (BioRRA) Study sought to identify predictors of drug-free remission in RA. 23/44 (52%) of participants in that study had an RA flare following DMARD cessation [5]. We will study an equivalent cohort of participants in the BIO-FLARE study, to allow us to understand the pathogenesis of flare in RA. Our hypothesis is that, consequent upon epigenetic influences, systemic immune factors integrate with the articular stromal compartment to provoke localised flare, supported and sustained by metabolic changes in the joint. We will use multivariate statistical techniques to develop models to elucidate the longitudinal relationship of potentially pathogenic pathways and identify those that are associated with impending relapse in RA, highlighting tractable therapeutic pathways and informative biomarkers.

Our hypotheses are based on our own published and ongoing studies, in extensive cohorts of early and established RA patients, which we will now apply to patients in remission [6–12]. The key biological question we are addressing is how the known pathways of RA pathogenesis trigger the transition from quiescent to active disease.

## Methods/design

### Study objectives

Our objectives are to carefully study our patient population to address the aforementioned knowledge gap. The primary objective of the study is to measure the immune dysregulation immediately prior to RA flare. In order to interrogate the biology of flare we will focus on:
Circulating immune cell subsets, their activation status and cytokine profilesAutoantibody profiles and other circulating mediatorsSynovial cellular subpopulationsMetabolic profiles related to immune and/or synovial activationEpigenetic profiles

The secondary objectives of the study are:
To corroborate baseline biomarkers predictive of sustained DMARD-free remission, as identified by the Biomarkers of Remission in Rheumatoid Arthritis (BioRRA) studyTo collect biological samples for future discovery researchTo establish the utility of physical activity monitoring (via accelerometry) to assist in the early detection of flare

### Study design

The BIO-FLARE study is a multi-centre, open-label, prospective, interventional, longitudinal cohort study undertaken at three academic rheumatology centres within the UK (Newcastle, Glasgow and Birmingham). The intervention is complete cessation of non-biological DMARDs (single or combination use of methotrexate, sulfasalazine and/or hydroxychloroquine). All participants who fulfil eligibility criteria will stop their DMARD therapy (without tapering). There is no randomisation involved. Participants will be followed up for 6 months after DMARD cessation or until the point of flare, whichever is sooner.

### Study population

The BIO-FLARE study aims to recruit 150 participants who stop DMARDs and complete the study over a 24-month period. After accounting for withdrawals and subjects who fail to meet the remission criteria, we estimate that we would need to recruit 181 participants to achieve our target (see Fig. 2). Participants may be identified via routine rheumatology outpatient clinics, or through existing databases.

**Fig. 2 Fig2:**
[figure not shown]
The BIO-FLARE Study overview with estimated patient numbers. Recruitment numbers are extrapolated from data observed in the BioRRA study [5] and other published studies of DMARD withdrawal [13, 14]. Sample collection will occur at baseline, 2, 5, 8, 12 and 24 weeks after DMARD withdrawal, and also at the time of arthritis flare if this occurs

Due to the SARS-CoV-2 pandemic, recruitment to the study was halted from March to August 2020 according to UK Department of Health guidance. After re-opening recruitment, participation remained low, and with increasing infection rates, there was low confidence that the recruitment numbers would improve. After extensive discussion that included trial statisticians, a decision was taken to close recruitment at 118 participants with complete data to enable timely analysis.

### Eligibility criteria

Inclusion criteria
I.Diagnosis of RA according to the 1987 ACR or 2010 ACR/EULAR classification criteria (applied at any time since diagnosis).II.Current single or combination use of methotrexate, sulfasalazine and/or hydroxychloroquine. No escalations in dose are permitted in the 6 months prior to enrolment, although dose reductions in this time are permitted.III.Arthritis currently in remission, as judged clinically by referring healthcare professionalIV.Patient and referring clinician willing to consider DMARD withdrawalV.Age 16 or over at time of symptom onset and 18 or over at time of recruitment

Exclusion criteria
I.Inability to provide informed consentII.Current participation or follow-up within another ongoing clinical interventional trialIII.Current pregnancy, or pregnancy planned within next 6 monthsIV.Major surgery planned within the next 6 months (at discretion of screening clinician)V.Immunisation within the past 4 weeksVI.Received oral, parenteral or intra-articular steroids within past 3 months (topical, inhaled and intra-nasal steroids are permitted)VII.Use of any DMARD other than methotrexate, sulfasalazine or hydroxychloroquine within the past 6 months (or past 12 months for leflunomide)VIII.Increase in the dose of any DMARD in the 6 months prior to screeningIX.Use of biologic therapy within the past 6 monthsX.Prior use of cell-depleting biologic therapiesXI.Haemoglobin < 9 g/L at baselineXII.Contraindication to synovial biopsy – e.g. bleeding diathesis or prolonged use of anticoagulant therapy (warfarin or other directly acting oral anticoagulants e.g. rivaroxaban)XIII.Active crystal arthropathy

### Screening visit

Participants attending a screening visit will have the opportunity to discuss the study further with an investigator before signing the consent form. At this point participants are also given the opportunity to consent to additional optional aspects of the study including a baseline synovial biopsy, stool sample collection for microbiome analysis and wearing an accelerometer (GT9X Actigraph) for the duration of the study to enable long-term physical activity monitoring.

Demographic information is collected including RA history, past medical history and medication history. A general physical examination is performed and participants complete questionnaires capturing patient reported outcome measures. Clinical and research blood samples are taken and a urine sample is obtained. A pregnancy test is carried out for women with child-bearing potential. A full list of the schedule of events at each visit is found in Table 1.

**Table 1 Tab1:** Schedule of events in the BIO-FLARE study

Procedures	Screening Visit	Day 0: Baseline (a) Telephone consultation	Day 0: Baseline (b) Synovial biopsy (OPTIONAL)	Day 14	Day 35	Day 56	Day 84	Day 168	Patient-requested ad-hoc study visits	Visit 2 weeks following ad-hoc study visit	Synovial biopsy assessment visit after flare confirmed
Discuss Study / confirm willingness to continue participation in study	X	X	X	X	X	X	X	X	X	X	X
Informed Consent for study	X										
Collect Demographics and medical history	X										
Record Current medication	X			X	X	X	X	X	X	X	
General Physical examination^a^	X										
Rheumatological Assessment - DAS28-CRP	X			X	X	X	X	X	X	X	
Instruction to discontinue DMARDs (if not opting for synovial Biopsy)		X									
Instruction to discontinue DMARDs (if opting for synovial biopsy)			X								
Patient Reported Outcome Measures / Questionnaires											
HAQ-DI	X							X	X	X	
RAPID-3	X			X	X	X	X	X	X	X	
EuroQol 5D-5L	X			X	X	X	X	X	X	X	
MFI	X							X	X	X	
RA-FQ	X			X	X	X	X	X	X	X	
FLARE-RA	X			X	X	X	X	X	X	X	
Blood tests											
Full Blood Count (FBC)	X			X	X	X	X	X	X	X	
Inflammatory markers (ESR & CRP)	X			X	X	X	X	X	X	X	
Antibodies (RhF & ACPA)	X										
Other clinical bloods (UE, LFT & Clotting)	X								X		
Research blood tests (Serum, EDTA, Tempus and Heparinised samples)	X			X	X	X	X	X	X	X	
Other research tests											
Urine Sample	X			X	X	X	X	X	X	X	
Pregnancy test^b^	X										
Stool Sample (OPTIONAL)	X			X	X	X	X	X	X	X	
Ultrasound assessment for Synovial Biopsy (OPTIONAL AT BASELINE – additional consent required)			[X]								X
Accelerometer provided^c^ (OPTIONAL)	X										
Activity diary provided (OPTIONAL)	X			X	X	X	X		X		

^a^Depending on the circumstances of the consultation, physical examination may be indicated at any study visit to establish whether DAS28-CRP reflects arthritis activity or infection etc. General Physical Examination is only mandatory at Screening

^b^Mandatory at Screening but should be performed at any visit subsequently if routine questioning suggests a participant may be pregnant. Serum or urine tests to be performed subsequently in line with local policy

^c^This may be provided after the study visit once eligibility confirmed, either by post, or at the optional Baseline Synovial Biopsy Visit (if applicable)

Following this visit, the disease activity score in 28 joints with C-reactive protein (DAS28-CRP) is calculated. The cut off for remission was set at DAS28-CRP < 2.4. This is lower than some other remission guidelines given the knowledge that DAS28 values calculated using CRP are commonly lower than those using ESR [15, 16]. If the DAS28-CRP score is < 2.4 and the participant has declined the optional baseline synovial biopsy, then the participant is advised to immediately discontinue their DMARD therapy. Participants who have a DAS28-CRP < 2.4 and have provided additional consent for an optional baseline synovial biopsy will be invited to attend for an additional biopsy visit at their regional Hub site. They will stop their DMARD treatment after the biopsy has been performed. If the DAS28-CRP score is ≥2.4 then the participant is withdrawn from the study at this point, they are referred back to their rheumatology team, and DMARD therapy is continued.

### Follow-up period – day 14, 35, 56, 84, 168 and ad hoc visits

At routine visits, adverse event recording and current medications are noted. Clinical and research blood and urine tests are taken and questionnaires are completed. A joint examination is performed to allow calculation of a DAS28-CRP.

If a participant feels that their arthritis is becoming more active during the follow-up period, then they can arrange an ad hoc visit. These visits follow the same format as the routine visits.

At any point in the study period if the participant is found to have a DAS28-CRP ≥ 3.2 they are defined as having a confirmed flare. If a participant is found to have a DAS28-CRP ≥ 2.4 but < 3.2 they will return for a further ad hoc assessment within 14 days. At the second assessment if the DAS28-CRP ≥ 2.4 they will be defined as a confirmed flare (Fig. 3).

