### Confirmed flare

If a participant has a confirmed flare (DAS28-CRP ≥ 3.2, or DAS28-CRP ≥ 2.4 on 2 occasions within 14 days) an ultrasound-guided synovial biopsy will be arranged to take place within 7 days of flare confirmation. Following the synovial biopsy, the participant will receive glucocorticoid therapy if needed, and will be discharged from the study back to their referring team to rapidly recommence DMARDs. A further review (telephone call or face to face visit) will occur 4 weeks after a confirmed flare to ensure the participants’ RA is back under control, that they have had contact with their referring rheumatology team, and that they have resumed DMARD therapy. No study data will be collected at that visit.

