### Clinical discretion

In certain circumstances, it may become clinically apparent that a participant has a DAS28-CRP ≥ 2.4 owing to an alternative clinical diagnosis other than their rheumatoid arthritis. Examples of this may include, but are not limited to:
I.Concurrent infection causing a rise in blood inflammatory markers or patient visual analogue scale leading to a rise in DAS28-CRP above remission thresholdsII.Local trauma event causing joint pain/swelling or a rise in patient visual analogue scale leading to a rise in DAS28-CRP above remission thresholds

In such circumstances, and after agreement with the participant, the research clinician has the discretion not to refer back to the clinical team for restart of DMARD therapy if this is felt to be clinically inappropriate. The participant should continue in the study, but should have an additional appointment review within 14 days. If the participant still has a DAS28-CRP ≥ 2.4 at this additional review, then they should normally be discharged from the study and restart their DMARDs via their referring clinical team.

Similarly, in some circumstances it may become clinically indicated to restart DMARD therapy despite the participant achieving a DAS28-CRP < 2.4 – for example, to control extra-articular manifestations of RA not measured in the remission criteria, or flaring in non-DAS28 joints, e.g. the ankles, feet. In these circumstances, the research clinician has the discretion to refer back to the clinical team for restart of DMARD therapy if this is felt to be clinically indicated at that time. The participant would then also be discharged from the study.

Furthermore, the clinician has the discretion to arrange additional investigations on clinical grounds as required in response to adverse events.

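### The flare definition rests on DAS28-CRP alone, but the clinical-discretion rule keeps some participants who meet it in follow-up, and the event status of those participants is not stated

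*Protocol article*

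**What the plan says.** Three sections of the protocol article bear on this.

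- **Follow-up period.** Of participants whose DAS28-CRP is 3.2 or more at any point in the study, it says that "they are defined as having a confirmed flare". A reading from 2.4 to below 3.2 leads to a further assessment within 14 days: "At the second assessment if the DAS28-CRP ≥ 2.4 they will be defined as a confirmed flare". Cause plays no part.
- **Confirmed flare.** The criteria are repeated as "DAS28-CRP ≥ 3.2, or DAS28-CRP ≥ 2.4 on 2 occasions within 14 days", again without exception. For these participants "an ultrasound-guided synovial biopsy will be arranged to take place within 7 days of flare confirmation", followed by discharge and resumption of DMARDs.
- **Clinical discretion.** This covers a score of 2.4 or more "owing to an alternative clinical diagnosis other than their rheumatoid arthritis", with infection and local trauma as examples. The clinician may decide not to refer the participant back for DMARD restart. "The participant should continue in the study, but should have an additional appointment review within 14 days". If the score is still 2.4 or more at that review, "then they should normally be discharged from the study and restart their DMARDs via their referring clinical team".

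Neither flare section refers to the discretion section, and the discretion section does not refer to the flare definition. Under Study design, follow-up ends at 6 months or at flare, whichever is sooner. Under Statistical considerations, time of flare feeds the Kaplan-Meier estimate at 24 weeks, and risk of flare is the outcome of the Cox or parametric marker models.

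**The concern.** Flare is the outcome of every analysis described under Statistical considerations, and the primary objective is to measure immune dysregulation just before RA flare. Among the discretion section's own examples is infection raising blood inflammatory markers and, through them, DAS28-CRP. If such a rise is counted as RA flare, markers of infection can appear as markers of flare. If the participant instead continues as not flared, the same visit contributes marker values to the at-risk comparison and may dilute a true association.

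The text also bears on what data exist. A confirmed flare leads to biopsy and ends follow-up; a participant kept in under discretion goes on giving samples. Two clinicians who each follow the article could therefore produce different outcomes, event dates and samples from the same readings.

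**Working it through.** **1. The two rules applied to the same readings.** Take a participant with a suspected non-RA cause and two readings, the first and the review within 14 days. The values are illustrative, chosen to fall in each band.

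| First / review | Flare sections | Clinical discretion section | Result |
|---|---|---|---|
| 2.6 / 2.0 | No flare, continues | Continues | Agree |
| 2.6 / 2.6 | Flare at second visit | Normally discharged; status and date not given | Status unstated |
| 3.4 / 2.0 | Flare at first visit | Continues; no flare implied | Direct contradiction |
| 3.4 / 2.6 | Flare at first visit | Continues, then normally discharged; status and date not given | Contradiction at first visit, then status unstated |

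Continuing implies not flared, because follow-up ends at flare. The direct contradiction is thus confined to a first reading of 3.2 or more. For a persistent reading after a first score below 3.2, the defect is an unstated outcome.

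**2. The document's own figure.** The 50% expectation rests on the earlier cohort: 23/44 = 0.523, which agrees with the stated 52%. No figure is in dispute.

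**3. Possible size.** The article does not say how many threshold crossings have a non-RA cause, so a range of 2% to 20% is assumed.

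Inputs: N = 118 (final recruitment) and an expected flare proportion of 50%, giving 118 × 0.50 = 59 threshold-defined flares. The 95% Wilson interval for 59/118 is 41.1% to 58.9%; the simple half-width is 1.96 × √(0.25/118) = 0.090.

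Let k be the number of the 59 that are non-RA. Counted as non-flare, the proportion is (59 − k)/118. Removed from the denominator, as a rough bound for early censoring, it is (59 − k)/(118 − k).

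| Assumed share | k | Counted as non-flare | Removed |
|---|---|---|---|
| 2% | 1 | 58/118 = 49.2% | 58/117 = 49.6% |
| 5% | 3 | 56/118 = 47.5% | 56/115 = 48.7% |
| 10% | 6 | 53/118 = 44.9% | 53/112 = 47.3% |
| 20% | 12 | 47/118 = 39.8% | 47/106 = 44.3% |

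At the low end the shift is under one percentage point. At the high end it is 50.0 − 39.8 = 10.2 points, about the half-width of the interval. The effect on marker coefficients cannot be computed from the article.

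**The case against.** The best defence is that the discretion section is a natural exception to a general rule. Its heading and opening mark special circumstances, and a footnote to the schedule of events foresees examination to tell arthritis activity from infection. On that view only a cross-reference is missing. Fig. 3, which is cited for the flare rule, is not shown and might mark the exception. Coding rules may also sit in the analysis plan or full protocol.

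Part of this stands. An override is a reasonable reading, and the absence of detailed censoring rules from a condensed article is not itself a fault. But both flare sections state their definition without exception, and nothing shown says which rule prevails. Even as an override, the discretion section leaves a persistent reading without an outcome, where the flare sections give it one.

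Several stronger readings are tempting and go too far:

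- *Every infection- or trauma-driven rise is classified in two ways.* A 2.6 / 2.0 pair is handled alike by both rules.
- *A persistent reading leads to exit without flare status or biopsy.* The section is silent on both and denies neither. Its discharge and DMARD restart match the end of the confirmed-flare pathway.
- *Such participants are coded as remission.* The section assigns no outcome label. For a participant who stays in and completes follow-up, non-flare status is an inference from the follow-up rule.
- *If 5% to 10% of all participants had an episode, the flare proportion would shift by 5 to 10 points.* The rate is assumed. The shift would also require every episode to meet the flare criteria and no affected participant to flare later, although about half are expected to flare.
- *The discretion introduces centre bias.* Three centres applying discretion could differ, but the article gives no evidence that they do.

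**Conclusion.** The point holds within limits. The flare definition and the discretion rule contradict each other directly for a first DAS28-CRP of 3.2 or more with a suspected non-RA cause. For a repeat reading of 2.4 or more handled under discretion, event status and date are unstated, while the flare sections would call it a flare. This is more than a missing detail: followed literally, the flare rule counts infection or trauma as RA flare in the outcome on which all the flare analyses depend.

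The size is unknown. The illustrated fall from 50% to between about 49% and 40% rests on 59 threshold-defined flares in 118 participants, an assumed non-RA share of 2% to 20%, and all of those being counted as non-flare. It shows what could follow from the ambiguity; it does not estimate how often such episodes occurred.

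**What to change.** Reconcile the Follow-up period, Confirmed flare and Clinical discretion sections into one endpoint rule. It should say whether an attributed non-RA cause affects flare status under each DAS28-CRP criterion, and give the event status and the event or censoring date for every participant handled under discretion. Which clinical rule should apply is for the trial team; this review takes no position on it.

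For the analysis:

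- Attribute readings to a non-RA cause from the visit and adverse event records already held, by assessors blind to research marker results. Recruitment has closed at 118 participants with complete data, so a new case report form field could not be filled in at visits already held.
- Whichever coding is primary (DAS28-CRP criteria alone, or adjusted for attribution), run the other as a sensitivity analysis.
- Exclude samples from illness-attributed visits in a sensitivity analysis only. Dropping them from the main marker analysis is debatable, since time-varying models can keep them and exclusion brings its own selection.

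The cost is a clarification, a small blinded record review and some extra model runs. One limit remains: the Adverse events section does not record joint pain, swelling or stiffness as adverse events, so trauma-related rises may be incompletely documented and harder to attribute than infections.
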